## **4.4 Implementation and psychometric criteria of clinical assessments**

### **4.4.1 Functional Gait Assessment**

The Functional Gait Assessment (FGA) (Wrisley et al., 2004) is used to assess dynamic balance during walking and evaluates a person's ability to perform multiple motor tasks while walking.

#### **4.4.1.1 Implementation**

The FGA consists of 10 items. The items address walking on a surface without a slope at different speeds, with head turns, with quick turns and stops, climbing stairs and climbing over obstacles. Individual items are scored on a scale of 0-3 points, with 3 points representing the best possible performance of the item. The total score is 30 points. The more points achieved, the better the dynamic balance of the test persons. The duration of the test is 5-20 minutes (Thieme et al., 2009).

#### **4.4.1.2 Psychometric criteria**

The MDC is 4 points (Petersen et al., 2017). For individuals with Idiopathic Parkinson's Syndrome, the cut-off value is  $\leq 18/30$  points for identifying an increased risk of falls. The sensitivity is 80.6% and the specificity 80.0%. (Yang et al., 2014). The inter-rater reliability (ICC=0.99; 95% CI = 0.99-1.00) and intra-rater reliability (ICC=0.99; 95% CI = 0.99-1.00) are both excellent (Yang et al., 2016). Test-retest reliability is also very good with an ICC value of 0.86 (Petersen et al., 2017). Cronbach's alpha is 0.94, indicating excellent construct validity. (Yang et al., 2016).

#### **4.4.2 Measurement of eye movements during items 5, 6 and 10 of the FGA**

Items 5, 6 and 10 of the FGA are used separately to record dynamic balance and eye movements (saccade speed, amplitude, latency, fixation duration). This measurement is done with Tobii Pro Glasses 3 as explained above.

#### **4.4.3 Mini Mental Status Test (MMST)**

The MMST (Folstein et al., 1975) is used to assess cognitive function (temporal and spatial orientation, memory, attention, speech and language comprehension, also reading, writing, drawing and arithmetic) and serves as a screening tool for this clinical study.

##### **4.4.3.1 Implementation**

The test consists of tasks and questions to assess the test person's cognitive function. A maximum of 30 points can be achieved, whereby a result  $\leq 20$  points can be assumed to indicate dementia. The cut-off point of 24 points reliably indicates dementia with high sensitivity and specificity. (Stuss et al., 1996). The test takes about 7 to 10 minutes to complete. (Folstein et al., 1975).

##### **4.4.3.2 Psychometric criteria**

The smallest measurable difference (MDC) for people with PD with mild neurocognitive impairment is 6.43 points, with the smallest measurable difference (MDC) for people with PD with severe cognitive impairment is 6.16 points (Lucza et al., 2015). The construct validity of the MMST is high, shown by significant correlations with the Dementia Rating Scale is 0.87 ( $p < 0.001$ ) (Aarsland et al., 2004). Studies have shown that the MMST can validly measure cognitive decline over a longer period of about 10 years. (Lessig et al., 2012).

#### **4.4.4 Timed-Up-and-Go (TUG)**

The Timed-Up-and-Go is used to assess functional mobility, which is a primary endpoint of this study. (Podsiadlo and Richardson, 1991). The TUG is used as an indicator of the risk of falling during everyday movement tasks. The performance of the activities transfer from sitting to standing, walking, as well as making a turn in space, going back to the chair and sitting down is tested. For locomotion in everyday life and for the reduction of the risk of falling, the abilities to transfer from sitting to standing and to make a turn in space are of decisive importance. (Cheng et al., 1998; Mong et al., 2010)..

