| DRKS ID                | As soon as the Ethics Committee has given its approval, registration in the DRKS or another primary registry is applied for in accordance with the WHO criteria.                                                                                                                                                                                                                                                                                                                                                                                                                                                                                                                                  |
| Study objective        | The study objective is to investigate the effects of an activity-based physiotherapy training programme with eye movement training compared to an activity-based physiotherapy training programme without eye movement training on dynamic balance, mobility with and without multi-task, static and dynamic balance walking speed, health-related quality of life, freezing of gait, fall-associated self-efficacy, depression and fall rate. The aim is also to explore the change in eye movements (saccade velocity, amplitude, latency, fixation duration) over the intervention period and to evaluate the feasibility of a larger randomised controlled trial using predefined parameters. |
| Primary endpoints      | 1.1 Dynamic balance measured by the Functional Gait Assessment (FGA)

1.2 Items 5, 6 and 10 of the FGA are additionally performed with eye-tracking glasses (Tobii Pro Glasses 3) for mobile measurement of eye movements (saccade velocity, amplitude, latency, fixation duration).                                                                                                                                                                                                                                                                                                                                                                                                        |

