### 2.3 Study objectives

Thus, four **study objectives** are pursued to deepen the knowledge on effectiveness:

1. Assessment of the effects on dynamic balance (primary endpoint)
2. Investigating the feasibility of a larger randomised controlled trial
3. assessment of the effects on functional mobility with and without manual multi-task, static and dynamic balance, walking speed, health-related quality of life, freezing of gait, fall-associated self-efficacy, depression and fall rate (secondary endpoints).

4. evaluation of the change in eye movements during the intervention, measured once a week in the intervention group over the intervention period.

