## 2.4 Null hypotheses

**Primary null hypothesis:** There is no difference between the effects of an everyday physiotherapy training programme with eye movement training and such a training programme without eye movement training on dynamic balance in people with idiopathic Parkinson's syndrome.

**Secondary null hypotheses:** There is no difference between the effects of an everyday physiotherapy training programme with gaze movement training and such a training programme without gaze movement training on functional mobility with and without manual multi-task, static balance, walking speed, health-related quality of life, freezing of gait, fall-associated self-efficacy, depression, fall rate and eye movements during dynamic balance tasks and specific training items in individuals with Idiopathic Parkinson's Syndrome.

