### 4.3.3 Primary and secondary endpoints and survey instruments

Table 2 lists the primary and secondary endpoints of the study with the respective survey instruments selected. All assessments are used in their validated German version. The implementation and psychometric criteria of the clinical assessments are described in chapter 4.4.

**Table 2:** Primary and secondary endpoints and survey instruments

| Endpoint                                                                                  | Survey                                                                                                       | Scr | BL | Int. | PI | FU
Call |
|-------------------------------------------------------------------------------------------|--------------------------------------------------------------------------------------------------------------|-----|----|------|----|------------|
| Primary clinical endpoints                                                         |                                                                                                              |     |    |      |    |            |
| Dynamic balance                                                                           | Functional Gait Assessment (FGA)                                                                             |     | X  |      | X  |            |
| Dynamic balance with eye movements (saccade speed, amplitude, latency, fixation duration) | Items 5, 6 and 10 of the Functional Gait Assessment (FGA) with mobile eye tracking using Tobii Pro Glasses 3 |     | X  |      | X  |            |
| Secondary clinical endpoints                                                       |                                                                                                              |     |    |      |    |            |
| Cognitive function                                                                        | Mini-Mental State Test (MMST)                                                                                | X   |    |      |    |            |
| Functional mobility                                                                       | Timed-Up-and-Go (TUG)                                                                                        |     | X  |      | X  |            |

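### The protocol contradicts itself on the primary endpoint: eye movements during three FGA items are primary in the synopsis and Table 2 but secondary in the hypotheses, and one stray sentence also calls the TUG primary

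*Protocol*

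**What the plan says.** The protocol labels endpoints in several places, and the labels differ.

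- **Objectives (2.3).** The first objective names one construct: "Assessment of the effects on dynamic balance (primary endpoint". Functional mobility appears in objective 3, among the secondary endpoints. Objective 4 concerns only the weekly recordings made in the intervention group during training.
- **Hypotheses (2.4, 2.5).** The primary null compares the programme with eye movement training against "such a training programme without eye movement training on dynamic balance in people with idiopathic Parkinson's syndrome". No instrument is named. The secondary hypotheses include functional mobility and, at the end of the list, "depression, fall rate and eye movements during dynamic balance tasks".
- **Synopsis.** Two primary endpoints are numbered: "1.1 Dynamic balance measured by the Functional Gait Assessment (FGA"), and, as 1.2, "Items 5, 6 and 10 of the FGA are additionally performed with eye-tracking glasses (Tobii Pro Glasses 3) for mobile measurement of eye movements", with four parameters: saccade velocity, amplitude, latency and fixation duration. The Timed-Up-and-Go (TUG) is secondary endpoint 2.1.
- **Table 2 (4.3.3).** The primary block holds the FGA and a second row: "Dynamic balance with eye movements (saccade speed, amplitude, latency, fixation duration"). TUG is in the secondary block. So is the Four Square Step Test (FSST), whose endpoint label is also dynamic balance.
- **Instrument description (4.4.4).** "The Timed-Up-and-Go is used to assess functional mobility, which is a primary endpoint of this study".
- **Analysis (5.6.1).** Significance is p<0.05. Bonferroni is mentioned only for the pairwise comparisons that follow a significant ANOVA.

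**The concern.** The same measurement, eye movements during the dynamic balance items, is primary in two places and secondary in two others. No reading makes both true. It also consists of four variables with no order among them.

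The construct in the primary hypothesis does not settle the matter by itself. Dynamic balance is not tied to an instrument in 2.4 or 2.5, and Table 2 uses the same term for the FSST, a secondary measure.

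At stake is which result is registered and reported as primary, and which endpoint sizes the later trial. Section 3.4 plans prospective registration after the ethics vote, and section 5.6.1 makes the pilot results the basis for that sample size calculation. An analysis plan takes its primary endpoint from the protocol, so it cannot resolve a protocol that gives two answers.

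**Working it through.** **1. Does the sample size identify the primary endpoint?** Section 4.1.2.3 uses N = n / (1 - z/100) with n = 30 and z = 10. This gives 30 / 0.9 = 33.3, rounded up to 34, which matches the stated figure. No endpoint, effect size or power enters the formula, so it gives no help.

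**2. Labels side by side.**

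| Measure | Synopsis | Table 2 | 2.3 | 2.4 and 2.5 | 4.4 |
|---|---|---|---|---|---|
| FGA | primary (1.1) | primary | dynamic balance: primary | dynamic balance: primary | no label |
| Eye movements, FGA items 5, 6, 10 | primary (1.2) | primary | not in the four objectives | secondary | no label |
| TUG / functional mobility | secondary (2.1) | secondary | secondary | secondary | primary (4.4.4) |
| FSST | secondary (2.4) | secondary, labelled dynamic balance | not named | not named | no label |

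The eye-movement row splits two against two. The TUG row is one sentence against every other passage.

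**3. Error rate if the primary list in the synopsis and Table 2 is followed.** Inputs: level 0.05 per test (5.6.1), taken as two-sided; one test for the FGA and one for each of the four eye parameters, so k = 5. One test per parameter is an assumption, because the protocol does not say how the three items are combined.

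- FGA alone: 5%.
- Five independent tests: 1 - 0.95^5 = 1 - 0.774 = 0.226, about 23%.
- Five correlated tests: the protocol gives no correlations, so a common correlation r was assumed. With Z_i = sqrt(r)·C + sqrt(1 - r)·E_i, where C and E_i are independent standard normal variables, the chance that the largest |Z_i| exceeds 1.96 (200,000 simulated draws) is:

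| r | At least one false positive |
|---|---|
| 0.3 | 21% |
| 0.5 | 18% |
| 0.8 | 13% |

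**4. After the fix.** With one primary endpoint the rate is 5%. Keeping all five would need 0.05 / 5 = 0.01 per test under Bonferroni.

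**The case against.** The strongest reply is that this is a pilot. Section 5.6.1 calls the inference preliminary and aimed at trends, and N = 34 comes from pilot-size rules plus 10% failure. No confirmatory claim depends on the 5% level. That stands, and it lowers the weight of the point. It does not remove the contradiction: the protocol states formal primary hypotheses and a significance level, and it uses the pilot to size the next trial.

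A second reply is that a rule for several primary endpoints may sit in an analysis plan that is not shown. That also stands. The absence of such a rule is not the point here; the conflicting labels are.

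A reader might infer more than the text supports, in three ways.

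- *TUG forms a third, rival set of primary endpoints.* It does not. Section 4.4.4 contains one clause in an instrument description, and the synopsis, Table 2, objective 3 and both hypothesis sections make functional mobility secondary.
- *The primary alternative could be claimed from TUG or from a saccade parameter.* It could not. Sections 2.4 and 2.5 confine the primary hypothesis to dynamic balance and place functional mobility and eye movements among the secondary hypotheses. Such a result could at most be labelled a primary endpoint.
- *The error rate is 26% (six tests) or 51% (14 tests).* These counts add TUG to the list, which merges conflicting versions that no passage presents together. The 14-test count also assumes that each eye parameter is tested separately in each of the three items, which no passage states. Both figures assume independence.

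**Conclusion.** The protocol is inconsistent on its primary endpoint. The substantive conflict is endpoint 1.2, which is primary in the synopsis and Table 2 and secondary in 2.4 and 2.5. The unnamed instrument in the primary hypothesis adds to it, since Table 2 applies the hypothesis term to the FSST as well. The TUG sentence in 4.4.4 is a separate and probably clerical error.

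If the longer primary list is followed, the chance of a false result labelled primary rises from 5% to roughly 13% to 23%. That range rests on one test per eye parameter and on correlations between 0.8 and 0. It describes results that could carry the primary label, not the error rate of the dynamic-balance hypothesis itself.

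This should be fixed. In a pilot with preliminary inference it does not undermine the study.

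**What to change.** - Name one primary endpoint throughout: change in FGA total score (0 to 30) from baseline to post-intervention. This follows objective 1 and the analysis in 5.6.1, which compares post-minus-baseline differences in ordinal scores between groups.
- In 2.4 and 2.5, put that wording in the primary hypotheses in place of dynamic balance, so that the FSST cannot fall under them.
- Move endpoint 1.2 to secondary in the synopsis and Table 2, which then match 2.4 and 2.5.
- Correct 4.4.4 so that TUG is secondary.

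The cost is wording in the synopsis, 2.4, 2.5, Table 2 and 4.4.4; data collection does not change. The downside is that an eye-movement result can no longer be presented as primary. If the sponsor wants to keep both endpoints as primary, the protocol must say so consistently and state how the 5% is shared, for example 0.01 for each of five tests.

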#### **4.4.4.1 Implementation**

The test starts in the seat, on a chair with a seat height of about 46 cm. To perform the TUG, the time it takes the test persons to stand up from the chair, walk a distance of three metres, turn around in the room, walk back the three metres to the chair and return to the starting position is recorded in seconds. The time required is documented in seconds. Aids that the test persons are currently using may be used. All aids used must be documented. The performance requires less than 5 minutes.

#### **4.4.4.2 Psychometric criteria**

The Standard Error of Measurement (SEM) is defined by Dal Bello-Haas and colleagues (2011) in people with idiopathic Parkinson's syndrome (Hoehn & Yahr stages 1-3) with 1.75 s. The smallest measurable difference (MDC) is 3.5 s. The smallest measurable difference (Minimal Detectable Change, MDC) is 3.5 s (Huang et al., 2011). The same authors report excellent test-retest reliability in people with idiopathic Parkinson's syndrome, with an ICC value of 0.80. The TUG has excellent test-retest reliability in people with idiopathic Parkinson's syndrome. The TUG has excellent inter-rater reliability and intra-rater reliability with ICC values of 0.99 and 0.98 respectively (Morris et al., 2001). In terms of criterion validity, very good values were achieved in persons with stroke in comparison with the Clinical Guideline System (CGS) ( $r = -0.86$ ), the Fast Gait Speed (FGS) ( $r = -0.91$ ) and the 6 Meter Walk Test ( $r = 0.92$ ). (Flansbjer et al., 2005).. For construct validity, Dal Bello-Haas described an excellent correlation with the Activities-specific Balance Confidence (ABC) Scale ( $r = -0.44$ ,  $p = 0.03$ ), and Bennie and colleagues (2003) an excellent correlation with the BBS ( $r = -0.47$ ,  $p = 0.04$ ). For predictive validity in individuals with Idiopathic Parkinson's Syndrome, Mak and Pang (2009) give Mak and Pang (2009) state that there is a significantly increased risk of falling with values  $>16$  s.

#### **4.4.5 Timed-Up-and-Go with manual dual task (TUGman)**

The timed-up-and-go with manual dual-task to assess fall risk is a secondary endpoint of this study. (Shumway-Cook et al., 2000). The TUGman is used as an indicator of the risk of falling during daily movement tasks with dual-task.

#### **4.4.5.1 Implementation**

The test starts in a seated position, on a chair with a seat height of about 46 cm. To carry out the TUGman, the time it takes the test persons to stand up from a chair, grab a glass of water, walk a distance of three metres with the glass in their hands, turn around in the room with the

glass in their hands, walk the three metres back to the chair, put the glass down and return to the starting position is recorded in seconds. The time taken is recorded in seconds. Aids that the test persons are currently using may be used. All aids used must be documented. The test takes 5 minutes to complete.

#### **4.4.5.2 Psychometric criteria**

The TUGman has excellent inter-rater reliability ( $r = 0.98$ ) and intra-rater reliability with an ICC value of 0.99. (Hofheinz and Schusterschitz, 2010). For criterion validity, Hofheinz and Schusterschitz (2010) described very good values in comparison with the BBS ( $r = -0.72$ ). For predictive validity in persons with idiopathic Parkinson's syndrome, the following values are given Maranhão-Filho and colleagues (2011) state that a difference of  $> 4.5$  s between TUG and TUGman indicates an increased risk of falling. Shumway-Cook and colleagues (2000) describe a prediction rate of 90% in the identification of older adults as fallers if they take more than 14.5 seconds to complete the TUGman.

#### **4.4.6 Berg Balance Scale (BBS)**

The BBS (Berg et al., 1989) is a common measurement tool in physiotherapy that can be used to check the balance ability of patients.

##### **4.4.6.1 Implementation**

The BBS includes 14 activities which the therapist observes and evaluates in terms of static and dynamic balance. The activities are based on actions of everyday life: Transfers from sitting to standing, standing to sitting and transferring (items 1, 4 & 5), static balance in standing and sitting without support, standing with eyes closed, standing with close foot position, reaching forward with both arms, picking up an object from the floor, looking over the shoulder while standing, turning once  $360^\circ$  while standing, tandem stand (One foot directly in front of the other) and single leg stand (items 2, 3, 6, 7, 8, 9, 10, 11, 13 & 14) and dynamic balance in standing by placing both feet alternately on a step (item 12). (Scherfer et al., 2006).

The 14 items are rated with the points 0-4. The value 0 describes that the patients can only perform the tasks with maximum help. 4 points, on the other hand, mean that the patients can perform the task without any problems. A maximum score of 56 points is therefore to be achieved. Berg et al. (Berg et al., 1989) divide the patients into three groups after the evaluation. A score of 0-20 indicates that the patient needs a wheelchair, 21-40 points indicate assistance with walking and 41-56 points indicate independent walking. The time required to complete the test is 15-20 minutes.

#### **4.4.6.2 Psychometric criteria**

The MDC is 5 points (Steffen and Seney, 2008a). The cut-off value of the BBS for an increased risk of falling is  $\leq 52/56$  points. (Schlenstedt et al., 2016).. The test-retest reliability and the inter-rater reliability are in a very good range with ICC values of 0.80 and 0.95, respectively. (Leddy et al., 2011). Franchignoni and colleagues demonstrated a high internal consistency (Cronbach's  $\alpha = 0.95$ ) in 70 people with idiopathic Parkinson's syndrome and an average Berg Balance score of 46.5 (34-54) points. (Franchignoni et al., 2005).. For criterion validity, Brusse and colleagues describe Brusse and colleagues (2005) describe very good values in comparison with the TUG ( $r = -0.78$ ) and the UPDRS ( $r = -0.64$ ).

